**Selection and enrollment of participants**

**Study Enrollment and Withdrawal**

One hundred two healthy male and female participants, ages 18-45 will be enrolled in two groups. It is estimated that 204 subjects will need to be screened (2:1 screened to eligible) to enroll 102 subjects. At screening/enrollment, subjects will be stratified as to whether they received inactivated or live influenza virus vaccination. Subjects will be recruited through customary IRB-approved methods. Children, pregnant women, prisoners and other vulnerable individuals will not be enrolled.

Screening will begin with a brief IRB-approved telephone screen. Information about the study will be presented to potential subjects. The telephone script will include the inclusion/exclusion criteria. Appointments will be made for subjects who are interested in the study at the Case Western Reserve University Dental School Room 3080 for further screening/enrollment procedures and protocol-specific information.

Study retention strategies will include education and explanations of the study schedule and procedures during enrollment. In addition, reimbursements will be dispersed at specified time points during the study with the amount contingent on completion of study procedures. Participants will be reminded before visits, and the clinical research study staff will contact participants who miss appointments to determine if they wish to return for further evaluation.

**Inclusion Criteria**

1. Signed informed consent

2. Ages between 18-45 years, inclusive

3. Non-tobacco/nicotine use (at least 3 months)

4. BMI of 17-35 kg/m^2^ inclusive

5. Able to comply with all study procedures and follow-up

6. Healthy on the basis of screening medical exam, blood chemistries, hematology,

and serum pregnancy tests for females (at screening )

7. Non-pregnant or breast-feeding

**Exclusion Criteria:**

1. History of current use of narcotics, or recreational drug use.
2. Use of > 7 alcoholic beverages in 1 week

2. Any acute illness such as asthma, cardiovascular, respiratory, hepatic, renal,

hematologic, gastrointestinal (including eating disorder), endocrine/metabolic,

neurologic, dermatologic, or psychiatric disease.

3. Treatment with another investigational product in the past 30 days

4. Immunocompromised status including HIV by history

5. Use of any other intra-oral product (especially antiseptic).

6. Intended use of mouthwash during study duration

7. Laboratory (screening) of creatinine > 1.5 X ULN, hemoglobin < 10.5 g/dL, platelet count ≤ 99,000/mm^3,^ absolute neutrophil count ≤1200/ mm^3^, serum glucose ≥ 150 mg/dl (Subject can enroll prior to receiving lab results. Subject will be contacted if lab results are an exclusion and discontinue from study)

8. Use of any systemic antibiotic or antifungal within 30 days of screening

9. Prior or current history of seasonal allergies, chronic sinusitis or rhinitis

10. Allergy to any component of Halo

11. Oral lesions

12. Dentures

13. Dental Treatment currently in progress (implants, root canals, complex

restorative procedures)

**Study Outcome Measures**

The **primary study objective** is to establish whether Halo will decrease the frequency, duration, and severity of acute respiratory disease and decrease the detection of respiratory viruses by multiplex PCR. After enrollment, subjects will be seen at scheduled monthly visits (+/- 7 days), 1-2 months after study completion and at interim visits when they develop a syndrome consistent with an acute upper respiratory disease. An acute upper respiratory disease will be defined as having fever to > 37.8°C and a non-productive cough and 2 or more of the following symptoms:

- Sore throat
- Rhinorrhea
- Sinus congestion
- Malaise

Patients will be provided with diaries (RedCap) to note any illness especially acute respiratory disease and to record the duration of each sign or symptom. Subjects will also be asked to take their temperature at 5p.m. each day and record their temperatures in the diaries. At interim visits related to the development of acute upper respiratory illness oropharyngeal swabs will be obtained for bacterial and fungal culture as well as respiratory virus multiplex PCR.

**Multiplex RT-PCR:** Following collection, an aliquot of the clinical sample will be placed in viral freezing media and stored at -80 degrees. Samples will be placed in 2ml glass collection tubes at a 1:1 ratio of clinical sample to viral freezing media. RNA from each clinical specimen will be extracted with the QiaAmp Viral RNA Mini Kit (Qiagen Inc., Valencia, CA) according to the manufacturer’s protocol. Extracted RNA will be stored at -80 degrees until processing.

Primers and probe sets for multiplex real-time RT-PCR detection of respiratory tract viruses have already been described [[35](#_ENREF_35)]. We will screen influenza positive samples under conditions as described with the exception that chlamydia and mycoplasma primer sets will be omitted. In addition, screening reactions for recently recognized viruses will be performed separately using real time primer sets as previously described [[36](#_ENREF_36), [37](#_ENREF_37)].

Microbial cultures will be performed from oral swabs obtained from enrolled study participants. Briefly, collected swabs will be vortexed in 1 mL saline, and a calibrated 10 µL inoculation loop will be used to spread the resulting suspension (and its serial dilutions) onto agar plates specific for aerobic or anaerobic bacteria (blood agar), or fungi (Sabouraud dextrose). Plates will be incubated at 37 °C overnight and the resulting CFUs will be counted to determine the microbial load.

In terms of safety and tolerance of Halo and placebo, the oropharynx and gingiva will be examined for erythema and ulcerations during each scheduled visit. This will not be pursued at the interim visits when presenting with an acute upper respiratory disease as mucosal changes are likely to be present related to these syndromes. Subjects will be queried about any intraoral or systemic adverse reactions. Toxicity will be graded according to modification of the National Institutes of Health, National Institute of Allergy and Infectious Diseases, DMID Adult Toxicity Tables provided in Appendix 1.

Subjects will keep a daily diary of oral temperature, product usage adherence, typical cold and flu symptoms that may occur, school or work absenteeism, and visits to physicians’ offices, emergency departments and urgent care centers using REDCap electronic data capture tools hosted at University Hospitals Case Medical Center. REDCap (Research Electronic Data Capture) is a secure, web-based application designed to support data capture for research studies. Following the completion of the study, participants will be asked to take a short survey through the same REDCap system in order to assess the acceptability of the product and to gather information about the volunteers’ willingness to continue to use the product beyond the study parameters and if they would recommend the product to others. Finally, to further assess adherence to the study, product bottles will be counted.

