**Protocol Schema**

A Pilot Study of the Safety, Tolerability, and Effectiveness of Halo to Prevent Acute Upper Respiratory Illness and Respiratory Virus Infections

**DESIGN** This is a randomized, double-blinded, placebo-controlled clinical trial

**DURATION** Participants will be on treatment for 75 days. A follow up visit will occur within 2 months after treatment ends.

**SAMPLE SIZE** 51 participants each in the treatment and placebo arms

**POPULATION** Healthy men and women 18 to 45 years old, inclusive

**INTERVENTION** Participants will be randomized with equal proportion (51 each) into one of the following 2 groups:

- Halo administered intra-orally by spray Three times daily
- Placebo administered intra-orally by spray Three times daily

**HYPOTHESIS** The use of Halo sprayed intra-orally three times daily

will be associated with fewer episodes and duration of acute

respiratory diseases and less frequent detection of important

respiratory viruses confirmed by multiplex PCR

**PRIMARY OBJECTIVES** 1. To establish whether Halo will decrease the

frequency of acute upper respiratory illness

2. To assess whether Halo will decrease the duration

and severity of acute upper respiratory illness

**SECONDARY**  1. To assess the tolerability, acceptability and adherence to

**OBJECTIVES** Halo

2. To compare whether acute upper respiratory disease in

those receiving Halo compared to placebo is associated with differences in absenteeism (from work or school) and visits to physicians’ offices, emergency departments and urgent care centers

3. To determine whether Halo will decrease

the detection of respiratory viruses by PCR

4. To evaluate the effect of Halo on bacterial and fungal

microflora in the oropharynx

5. To evaluate the effect of Halo on those who did and did not receive the influenza vaccine.

**ENDPOINTS** 1. Frequency and duration of clinical respiratory disease at

interim visits and assisted by patient diaries

2. Intra-and extra-oral exams

3. Solicited and unsolicited adverse events

4. Respiratory virus multiplex PCR

5. Bacterial (oral streptococci, Group A streptococcus) and

fungal cultures

6. Bottle counts and self-report for adherence

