**Interim Analysis**

We will carry out an interim analysis when all the patients recruited have been followed for one and a half months. Since this is a pilot study, this analysis will be carried out at a stringent level of significance.

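### PCR detection is primary in one section and secondary in another, and the two primary outcomes with a stated test share one alpha of 0.05 with no order or split

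*Protocol*

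**What the plan says.** **Tier of each outcome.** The Protocol Schema has two primary objectives. The first concerns the "frequency of acute upper respiratory illness"; the second covers how long an illness lasts "and severity of acute upper respiratory illness". Secondary objective 3 in the same list concerns "the detection of respiratory viruses by PCR". The section on outcome measures words the primary aim differently, asking "whether Halo will decrease the frequency, duration, and severity of acute respiratory disease and decrease the detection of respiratory viruses by multiplex PCR". That sentence adds PCR detection to the primary tier.

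**Tests and alpha.** Sample Size Calculations takes alpha as 0.05 for primary outcomes in the plural. It gives assumptions for two: events (2 against 1.5, SD 1) and duration (4 against 3 days, SD 2). The Statistical Analysis section names t-tests for those same two. Neither section gives an assumption or test for severity or for PCR detection.

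**Interim.** An interim analysis takes place "when all the patients recruited have been followed for one and a half months", and "this analysis will be carried out at a stringent level of significance". No number is given.

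**The concern.** A protocol should let a reader say, before any data are seen, which result decides whether the trial succeeded. This one does not, for two reasons.

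First, the tier of PCR detection depends on the section read. A favourable PCR result could be presented as primary and an unfavourable one as secondary, and either choice could cite the protocol.

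Second, two outcomes are primary and each has a planned t-test, but only one alpha is stated. Nothing says which test comes first, how 0.05 is divided, or whether both must succeed. If success on either one counts, the error rate for a primary claim is above 5%.

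**Working it through.** **The plan's own figures.** The protocol states no overall error rate, so there is none to reproduce. The one figure tied to its alpha is the base sample size of 23 per group. The standardised difference is 0.5/1 = 0.5 for events and 1/2 = 0.5 for duration. At two-sided 0.05 and 80% power, the normal approximation gives n = 2 × (1.960 + 0.842)² / 0.5² = 62.8, so 63 per group (64 with the t distribution). The 23 does not follow from these inputs. That is a separate matter: the error rates below depend only on alpha, the number of tests and their correlation.

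**Inputs.**
- Alpha 0.05: Sample Size Calculations. Sidedness is not stated; two-sided is assumed.
- Primary outcomes with a stated test: two, events and duration, from Sample Size Calculations and Statistical Analysis.
- Correlation between the two test statistics: not given. Assumed range 0 to 0.8.

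**Step 1: two tests, each at 0.05, success on either.** If independent, the error is 1 − (1 − 0.05)² = 1 − 0.9025 = 9.75%. If correlated, it is 1 − P(|Z₁| ≤ 1.96 and |Z₂| ≤ 1.96), with (Z₁, Z₂) bivariate normal.

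| Correlation | Chance of at least one false positive |
|---|---|
| 0 | 9.75% |
| 0.5 | 9.1% |
| 0.8 | 7.8% |

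Whatever the correlation, the rate cannot exceed 2 × 0.05 = 10%.

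**Step 2: upper scenarios.** If severity were also tested at 0.05 and all tests were independent: 1 − 0.95³ = 14.3%. If PCR detection were added as well: 1 − 0.95⁴ = 18.5%. In simulation with pairwise correlation 0.5, the figures are 12.6% and 15.6%; with 0.8, they are 9.8% and 11.4%. The protocol states no test for the third and fourth outcomes, so these rates do not follow from its text.

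**Step 3: the interim look.** Taking one and a half months as 45 of the 75 treatment days gives an information fraction of 45/75 = 0.6. This is an assumption; staggered enrolment would raise it and make the look cost less. The correlation between interim and final statistics is √0.6 = 0.775. For one outcome with the final test at 0.05, the overall two-sided error is 5.01% with the interim at 0.001 and 5.3% with the interim at 0.01.

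**Step 4: splitting alpha or ordering the tests.** With 51 per group and a standardised difference of 0.5, two-sided t-test power is 70.6% at alpha 0.05 and 60% at 0.05/2 = 0.025. A fixed sequence keeps the first outcome at 0.05, so it loses no power.

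**The case against.** The strongest reply has four parts.

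*The trial is a pilot that also aims at estimates with confidence intervals, and a multiplicity rule may sit in an analysis plan that is not shown.* This stands in part. The lack of an adjustment rule would not be a finding by itself. But the protocol also plans significance tests and sets out to establish an effect. An alpha rule in another document would have to act on a list of primary outcomes that the protocol states in two incompatible ways.

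*Four outcomes are not each tested at 0.05.* Correct. A reader might infer an 18.5% error rate from the four components of the primary objective. The documents do not support that: tests are stated only for events and duration. Independence is also unlikely, because all four outcomes arise from the same illnesses.

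*Severity can be studied.* A reader might infer that it cannot, because Study Outcome Measures asks participants "to record the duration of each sign or symptom" and mentions no rating. But the Overview says severity is captured daily by diary. The diary also holds temperature, symptoms, absenteeism and care visits, and Interim Visits adds hospitalisation. What remains is narrower: severity is called primary, yet no assumption or test accompanies it.

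*The interim look adds little.* Correct. A reader might count it as a further serious source of error, but at a level that deserves the word stringent it adds 0.01 to 0.3 percentage points for one outcome. Its missing number is a detail that an analysis plan could supply.

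**Conclusion.** The point holds in a limited form. The contradiction over PCR detection is certain from the text and leaves its tier open to choice after the data are seen. For the two primary outcomes that have a stated test, the chance of at least one false-positive primary result is about 8% to 10%, roughly 1.6 to 2 times the nominal 5%. This assumes two-sided tests, each at 0.05, success on either counting as a primary result, and a correlation between 0 and 0.8. The 18.5% figure would apply only if severity and PCR detection were also tested without adjustment and all four tests were independent. The unquantified interim level is a clarification and carries no weight in this conclusion.

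**What to change.** 1. Name the number of acute upper respiratory illness episodes per person as the single primary outcome, tested at two-sided 0.05.
2. Test average duration of illness next in a fixed sequence: at two-sided 0.05, and only if the first test succeeds.
3. Give PCR detection the same tier in the Protocol Schema and in Study Outcome Measures. Secondary matches the Schema's objectives list.
4. List severity as secondary in both sections, since no assumption or test accompanies it. The diary and care-visit data can still describe it.
5. If the interim analysis is kept, state its level and outcome. Two-sided 0.001 on the primary outcome, with the final test at 0.05, leaves the overall error at about 5.01% at 60% information.

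The cost is protocol wording only: no added participants, visits or data fields. The sponsor gives up the right to call several outcomes primary, and duration can be claimed only after a positive result on episodes. Power for the first outcome is unchanged, whereas splitting alpha in two would lower it from 70.6% to 60% at 51 per group.

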**Scheduled Follow-up Visits**

At these visits, an interval medical and concomitant medication history will be obtained. Solicited and unsolicited adverse reactions will be ascertained. The study diaries will be reviewed with participants. An oropharyngeal exam will be conducted by study clinicians and a fuller symptom-directed physical exam will be performed if indicated. The intra-oral examination will be performed by utilizing the diagram provided in Appendix 3. A posterior pharyngeal and nasal swab will be obtained at each visit to ascertain bacterial and fungal organisms and a multiplex PCR for respiratory viruses. The enrollment and interim visit pharyngeal and nasal swabs will be analysed in real time, all other swabs will be stored for future use determined by funding. Study bottles will be collected and counted. Study product will be provided until the next scheduled visit, study procedures will be again reviewed, and contact information for reaching study personnel will be revisited. Appointments for the next monthly evaluation will be made.

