**Interim Visits**

Subjects will be instructed to contact study personnel in the event they develop an acute upper respiratory disease as defined above within 72 hours of onset of symptoms and signs (this allows for weekends and holidays). At these visits, an interval medical and concomitant medication history will be obtained. Solicited and unsolicited adverse reactions will be ascertained. An oropharyngeal exam will be conducted by study clinicians and a fuller symptom-directed physical exam will be performed if indicated. If pharyngitis with exudate is observed or suspected, a rapid group A streptococcal (GAS) screen will be performed. Subjects positive for Group A streptococcal infection will be given a prescription for appropriate antibiotics and a referral for follow-up care as needed. If individuals present with symptoms and signs of acute influenza fever, sore throat, myalgias, headache and chills, they will be tested for influenza and prescribed Tamiflu as needed. A posterior pharyngeal and nasal swab will be obtained to ascertain baseline bacterial and fungal organisms and a multiplex PCR for respiratory viruses. Any visit to a physician’s office, emergency department, urgent care center or the need for hospitalization will be recorded. Subjects will be carefully instructed to record the duration of each symptom and sign to be recorded in the study-supplied diaries.

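### Fever is mandatory for a primary event, but only one 5 p.m. temperature a day is scheduled, so a short or treated fever can go uncounted and its PCR sample can be lost

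*Protocol*

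**What the plan says.** Study Outcome Measures makes fever a required element of the event: "An acute upper respiratory disease will be defined as having fever to > 37.8°C and a non-productive cough and 2 or more of the following" (sore throat, rhinorrhea, sinus congestion, malaise). The same section sets the temperature schedule: "Subjects will also be asked to take their temperature at 5p.m. each day and record their temperatures in the diaries".

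The diary is broader than the event definition. Study Outcome Measures says "Patients will be provided with diaries (RedCap) to note any illness especially acute respiratory disease and to record the duration of each sign or symptom", and later "Subjects will keep a daily diary of oral temperature, product usage adherence, typical cold and flu symptoms that may occur". It goes on to list absenteeism and health-care visits. Antipyretic use is not listed. Scheduled Follow-up Visits adds "The study diaries will be reviewed with participants", and a concomitant medication history is taken at scheduled and interim visits.

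The illness visit starts with the participant. Interim Visits says "Subjects will be instructed to contact study personnel in the event they develop an acute upper respiratory disease as defined above within 72 hours". The Protocol Schema takes frequency and duration at "interim visits and assisted by patient diaries". Under Scheduled Follow-up Visits, only enrolment and interim-visit swabs are analysed in real time. The others are stored, and their use depends on funding.

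**The concern.** A required criterion is only as good as its measurement. Cough, sore throat and malaise can be reported for the whole day, but fever counts only if a thermometer was used while it was present. A participant who is febrile overnight, or who takes an antipyretic some hours before 5 p.m., may record a normal value on a day with true fever. If no other reading is taken, the illness fails the definition.

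Two losses follow. The episode drops out of the primary count, and the participant, applying the full definition at home, has no reason to call. The interim visit and its real-time PCR sample then do not happen, so the virus-detection objective loses the same episode. Neither loss can be repaired in the analysis, because a temperature never taken and a swab never collected leave no data.

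**Working it through.** **Inputs from the protocol.** Fever above 37.8°C is mandatory, and one reading is scheduled every 24 hours (Study Outcome Measures). Sample Size Calculations gives mean events of 2 (control) and 1.5 (treated) with SD 1, illness duration of 4 vs 3 days, alpha 0.05, 80% power, and 23 per group raised to 51.

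**Input not in the protocol.** The fraction *s* of true febrile illnesses that are captured. No fever duration is given either. Both are assumed below, over a range.

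**Step 1: the plan's own figure.** The normal approximation is n = 2(z₁₋α/₂ + z₁₋β)² SD²/δ². With δ = 0.5 and SD = 1 this gives 2 × (1.96 + 0.84)² / 0.25 ≈ 63 per group two-sided, or 50 one-sided. The stated 23 does not reproduce. That is a separate matter; here it only fixes the baseline. Two-sided power at 51 per group with no loss is 71%.

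**Step 2: capture by one reading a day.** Assume one continuous fever of D hours with onset at a random clock time. The chance that at least one reading falls within it is min(1, D/24).

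| D (hours) | Capture |
| --- | --- |
| 8 | 8/24 = 33% |
| 12 | 12/24 = 50% |
| 18 | 18/24 = 75% |
| 24 or more | 100% |

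Recurrent fever raises capture. If a 12-hour fever returned on three days at independent clock times, capture would be 1 − 0.5³ = 88%. A late-afternoon temperature peak would raise it further. An antipyretic taken before the reading would lower it.

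**Step 3: effect on counts and power.** Apply the same *s* to both arms. Means become 2s and 1.5s, so the expected difference is 0.5s and the ratio is 1.5s/2s = 0.75 for every *s*. Losing events at random also changes the spread, so two versions of the SD are used: held at 1, or with variance s²·SD² + s(1 − s)·mean, averaged over arms. At s = 0.8 the averaged variance is (0.96 + 0.88)/2 = 0.92, giving SD 0.96.

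| s | Means | Expected difference | Two-sided power at 51 per group (SD 1 / SD recalculated) |
| --- | --- | --- | --- |
| 1.0 | 2.0 vs 1.5 | 0.50 | 71% / 71% |
| 0.9 | 1.8 vs 1.35 | 0.45 | 62% / 64% |
| 0.8 | 1.6 vs 1.2 | 0.40 | 52% / 56% |
| 0.5 | 1.0 vs 0.75 | 0.25 | 24% / 33% |

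These rows show sensitivity to *s*; they do not predict it. They also read 2 and 1.5 as true febrile illnesses. Sample Size Calculations does not say whether those means are true or recorded events. If they are recorded events, the loss is already inside them.

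**The case against.** A fixed daily reading is a defensible, standardised choice for a pilot, and several provisions limit the loss.

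- The protocol forbids no extra readings, and nothing says that the fever criterion uses the 5 p.m. value alone. Diaries are to record how long each sign lasts, and fever is a sign.
- An illness of the planned 3 to 4 days meets three or four 5 p.m. readings, and the 72-hour contact window holds about three. These are illness days, however, not fever days.
- Participants apply a written definition, not a free judgement. Study Outcome Measures describes interim visits more loosely, for a syndrome consistent with the disease, and Interim Visits provides for influenza-like presentations.
- Staff review the diaries, so an episode with a recorded fever but no interim visit can still be identified. The Schema's visits-plus-diary wording and the Overview's daily diary capture are complementary. A reader might see a contradiction about the source of an event, but the texts do not support that. How events are derived from diary and visit is commonly left to the SAP.
- Antipyretic use is not wholly uncollected, because concomitant medication is asked about at visits. Such a history need not show whether a dose preceded a particular reading.

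Most of this stands and limits the claim. What it does not answer is narrower: no provision asks for a temperature at the times when a short or treated fever would show, and diary review cannot recover a fever never measured or a swab never taken.

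**Conclusion.** The point holds as a weakness in measuring the primary event. A short or treated fever that is absent at 5 p.m. and not otherwise measured can go uncounted, and its real-time PCR sample can be lost as well.

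The size is unknown. Under the single-block, random-onset assumption, capture is 50% at 12 hours, 75% at 18 hours and complete from 24 hours. At an assumed 80% capture, equal in both arms, two-sided power at 51 per group falls from 71% to between 52% and 56%, and the rate ratio is unchanged.

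Two stronger readings are tempting and are not supported. A reader might infer that true febrile illnesses will be missed in quantity, but the protocol gives neither fever durations nor a capture rate, and fevers lasting a day or recurring over several days are largely caught. A reader might also infer bias between arms, because participants could guess their allocation and call or medicate differently, or because a product that shortens fever would make it harder to catch. Either is possible in principle, but the protocol has no data on guessed allocation, behaviour by arm or fever length, so unequal loss remains conjecture.

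**What to change.** - Keep the 5 p.m. reading every day, so that the standard series is preserved.
- On any day with a listed symptom, also ask for a temperature at symptom onset, in the morning and evening, and before any antipyretic dose the participant takes.
- Add an antipyretic yes/no item to the REDCap diary.
- State that the fever criterion uses the highest reading of the day.

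The cost is a few extra diary fields on sick days, with the same instruction in both arms. The change must be in place before enrolment, since missed readings cannot be reconstructed.

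Optionally, ask participants to contact staff at the first listed symptoms, so that staff apply the definition. This protects the PCR sample. It is a trade-off, because it brings some extra calls, and possibly swab visits, for illnesses that turn out not to qualify.

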**Experimental Design and Methods**

**Overview**

This is a pilot study of the safety, tolerability, and effectiveness of Halo to prevent acute upper respiratory illness and respiratory virus infections. This study will be conducted at one site (University Hospitals Case Medical Center) in healthy adults during the upcoming respiratory virus season. The intervention will be with Halo, a commercial product which is FDA-approved for the treatment of xerostomia. The placebo will consist of purified sterile water without CPC - the active antiseptic. This placebo was chosen as the Halo formulation without CPC serves to act as a barrier to attachment of oral pathogens, and as such is an important contributing factor to its antimicrobial activity (see above). The use of preservative could be problematic as there may be some anti microbial activity. Without the use of preservatives, the product will be refrigerated except for administration.

Male and female participants 18-45 years of age will be recruited and monitored for the development of, duration, and severity of clinical symptoms and signs consistent with acute respiratory disease (defined below) captured daily through diaries, and PCR confirmation of important respiratory viruses including influenza, rhinoviruses, adenoviruses, and respiratory syncytial virus during episodes of acute respiratory disease during the length of the study will be undertaken. Secondary objectives will assess the tolerance, acceptability and adherence to Halo as well as the change in the bacterial (oral streptococci and Group A streptococcus) and fungal microflora in the oropharynx. School or work absenteeism, visits to physicians’ offices, emergency departments and urgent care centers will also be captured. Conventional cultures for these bacterial and fungal organisms will be pursued (see below). Throughout the study period, the safety, tolerability, acceptability and adherence to study products will be assessed.

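### The multiplex PCR sentence limits the panel to influenza-positive samples, against the rest of the protocol, and routine follow-up swabs have no committed analysis

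*Protocol*

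**What the plan says.** **PCR.** The assay description in Study Outcome Measures states: "We will screen influenza positive samples under conditions as described with the exception that chlamydia and mycoplasma primer sets will be omitted". The next sentence adds that "screening reactions for recently recognized viruses will be performed separately using real time primer sets", with no influenza condition of its own. Earlier the same section says that "RNA from each clinical specimen will be extracted", and that "At interim visits related to the development of acute upper respiratory illness oropharyngeal swabs will be obtained for bacterial and fungal culture" as well as for multiplex PCR. The Overview plans "PCR confirmation of important respiratory viruses including influenza, rhinoviruses, adenoviruses, and respiratory syncytial virus during episodes of acute respiratory disease". Screening/Enrollment, Scheduled Follow-up Visits and Interim Visits each name multiplex PCR as a purpose of the swab, again without an influenza condition.

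**Routine swabs.** Scheduled Follow-up Visits first gives culture and multiplex PCR as the purpose of the swab at each visit. It then says that enrolment and interim swabs are analysed in real time, while "all other swabs will be stored for future use determined by funding". Appendix 2 places swabs at enrolment, V1, V2 and V3, with none at the final visit.

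**Objectives.** Virus detection by PCR is the third secondary objective in the Protocol Schema but part of the primary objective in Study Outcome Measures. The fourth secondary objective opens "To evaluate the effect of Halo on bacterial and fungal" and concerns the flora of the oropharynx; the Overview describes it as a change in that flora.

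**The concern.** Two things are at stake, and they are separate.

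First, the sentence that governs what the laboratory runs is narrower than the endpoint it serves. A laboratory working from it would put only influenza-positive material through the panel. The between-arm count of virus-positive illnesses would then lose illness due to the other named viruses, in an outcome that one section treats as primary.

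Second, if only enrolment and illness-visit swabs are analysed, every committed post-baseline culture comes from a participant who is ill. Illness is the outcome the spray is meant to change, so those participants are selected after randomisation by a variable treatment may affect. Comparing the flora of ill Halo users with that of ill placebo users is not a randomised comparison, and it says nothing about flora in users who stay well. The protocol follows similar reasoning elsewhere: Study Outcome Measures omits the safety examination of the mouth at illness visits because the illness itself is likely to alter the mucosa.

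Both matters concern which specimens are assayed. No analysis plan can recover a result that was never generated.

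**Working it through.** **PCR scope, statements side by side**

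| Place in the protocol | Which samples get the multiplex panel |
| --- | --- |
| Overview | Illness episodes; influenza, rhinoviruses, adenoviruses, RSV |
| Study Outcome Measures, interim swabs | All illness-visit swabs |
| Screening/Enrollment | Enrolment swab |
| Scheduled Follow-up Visits | Swab at each visit, then only enrolment and interim swabs analysed |
| Interim Visits | Illness-visit swab |
| Study Outcome Measures, assay sentence | Influenza-positive samples |

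The assay sentence stands alone against the other five. Its condition is also not defined for most samples: the only influenza test described outside the panel is in Interim Visits, for participants who present with influenza-like signs. Enrolment swabs and other illness swabs have no prior influenza result on which to select.

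**Routine swabs, counts**

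Inputs: 51 per arm, 102 in all (Protocol Schema); swabs at enrolment, V1, V2 and V3 (Appendix 2); planning means of 2 and 1.5 events per person (Sample Size Calculations). The count assumes full attendance and one illness visit per assumed event.

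- Enrolment, analysed: 102 × 1 = 102.
- Scheduled V1 to V3, stored: 102 × 3 = 306.
- Illness visits, analysed: 51 × 2 + 51 × 1.5 = 102 + 76.5 = 178.5.
- Share of post-baseline swabs with no committed analysis: 306 / (306 + 178.5) = 306 / 484.5 = 63%.

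The remaining 37% all come from illness episodes. A participant with no episode contributes no analysed post-baseline sample.

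**Which scheduled swabs are on treatment**

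Treatment lasts 75 days (Protocol Schema) and visits are monthly, within 7 days either way (Study Outcome Measures). Visit days are not stated; I assume a 30-day month.

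- V1: 30 ± 7, days 23 to 37.
- V2: 60 ± 7, days 53 to 67.
- V3: 90 ± 7, days 83 to 97, which is 83 − 75 = 8 to 97 − 75 = 22 days after the last dose.

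On that reading V1 and V2 are on treatment (102 × 2 = 204 swabs) and V3 is not.

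**What each objective is left with, once the assay sentence is corrected**

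| Question | Committed post-baseline data |
| --- | --- |
| PCR-positive illness per randomised participant | Yes, from illness-visit swabs |
| Virus detection without symptoms | None |
| Microflora in all randomised participants | None |
| Microflora during illness | Yes, but selected by the outcome |

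**The case against.** The strongest reply is that the PCR restriction is a slip, not a design. One sentence conflicts with several others, RNA is extracted from every specimen, and deleting two words cures it. That stands, and it is why this is a contradiction to reconcile and not evidence of a settled plan to test only influenza-positive samples.

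A reader might go further and infer that the virus-detection objective cannot be answered, or that non-influenza detections would be nil except as co-infections. The documents do not support either. The separate reactions for recently recognized viruses carry no influenza limit. The Overview places PCR confirmation within illness episodes, and those swabs are committed to analysis. With the wording corrected, PCR-positive illness per randomised participant is a valid between-arm comparison. Only detection without symptoms is left without data.

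A reader might also treat all 306 stored swabs as on treatment and propose culturing V3 as an end-of-treatment sample. That is not secure, because V3 may fall one to three weeks after dosing stops.

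Nor can the number of participants with an illness swab be derived from the planning figures. A Poisson model would give 51 × (1 − e^−2) ≈ 44 and 51 × (1 − e^−1.5) ≈ 40 per arm. But a Poisson mean of 2 implies an SD of 1.41, and the protocol plans an SD of 1.

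Finally, this is a pilot. Its sample size and named tests concern event counts and duration, the microflora objective is secondary, and the routine swabs are stored openly pending funds. This limits the weight of the second issue. It does not supply the missing comparison.

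**Conclusion.** The point holds in two parts.

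1. The assay sentence contradicts the protocol's own PCR scope and must be corrected. Taken literally, the panel would not detect rhinovirus, RSV or adenovirus illness without influenza. This rests on the text alone and needs no numerical assumption.

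2. Up to 306 scheduled swabs, about 63% of post-baseline swabs at the protocol's planning event means, have no committed analysis. Symptom-free virus detection and an unselected between-arm microflora comparison are therefore unsupported as planned. The 306 assumes full attendance; the 63% also assumes one illness visit per event. The conclusion depends on neither, because it follows from which visits are analysed.

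The first part is the more pressing, since it governs the measurement of an outcome that one section calls primary. The second limits what objective 4 can claim.

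**What to change.** **PCR.** Delete the words *influenza positive* from the assay sentence, so that every enrolment and illness-visit swab receives the full panel. Define the virus comparison as PCR-positive illness episodes per randomised participant, with 0 for a participant who has no illness. The cost is a wording change; the panel on these swabs is already planned elsewhere in the protocol.

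**Routine swabs.** Choose one of two courses.

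- Restate objective 4, and virus detection on routine swabs, as exploratory and conditional on funding, and state that no between-arm microflora claim will be drawn from illness swabs. This costs wording only.
- If funds allow, commit to culturing one already collected scheduled swab that is clearly on treatment, V1 or V2, in both arms. This adds 102 cultures at full attendance and no new sampling. V3 should not be the sole choice unless its visit day is shown to fall within the 75 days.
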